### Statistical analysis

Statistical analyses will be performed using SAS version 9.2 (SAS Institute Inc. Cary NC) and R version 2.11 (R Foundations for Statistical Computing). Baseline characteristics will be summarised using descriptive statistics. Continuous variables will be described as numbers of observed and missing values, mean, standard deviation, median, minimum and maximum. Categorical variables will be described as frequencies and percentages. Treatment evaluation will be performed on the principle of intention to treat (ITT), using data collected from all randomised participants. Analysis of covariance (ANCOVA) regression model will be used to evaluate the main treatment effect on the primary outcome between the two treatment groups, adjusting for its baseline measure, age, ethnicity and other potential confounding factors (if they are statistically significant at 5% level). A similar approach will be used for other continuous secondary outcome measures. Logistic regression model will be considered for the analysis of a binary outcome (e.g. meeting physical activity recommendations).

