### Sample size calculation

The target sample size of 162 participants (81 per group) will provide 80% power at 2.5% level of significance (one-sided) to show that the REMOTE and standard exCR programs do not differ by more than ml⋅kg^-1^⋅min^-1^ on peak oxygen uptake (V̇O_2_max). This sample size is based on the assumption the standard exCR program will result in an increase of 2.4 ml⋅kg^-1^⋅min^-1^ (SD =2.7) in V̇O_2_max, and has been inflated to allow for 10% loss to follow up [12]. The non-inferiority margin was chosen because it is clinically significant and is associated with lower CV-mortality [41, 42].

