### Randomisation and blinding

After written consent is obtained, baseline assessment is completed and then participants are randomised using sealed sequential, opaque envelopes. Participants are randomly allocated to either the control (traditional exCR) or intervention (REMOTE) arms at a 1:1 ratio, stratified by study site and sex. The allocation sequence is overseen by the project statistician (YJ). Assessors of the primary outcomes are blind to treatment allocation; however participants are not blind.

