## Discussion

This novel study evaluates a supervised exercise program delivered via a mobile phone and sensor system compared to a traditional model of supervised exCR. Remote monitoring may offer the same benefits as supervised gym-based programs, but is potentially more accessible to a broader range of patients and is cost-effective.

The protocol, in accordance with the SPIRIT statement, incorporates findings from recent mobile and telehealth systematic reviews, with the aim of building on this empirical evidence. The REMOTE-CR trial includes an objective assessment of maximal cardiorespiratory fitness, which is the gold standard measurement following exCR. It also includes objective assessment of physical activity, which was lacking in previous research [34].

The non-inferiority trial design is most suitable because it is unlikely the REMOTE intervention will result in substantially greater improvement in exercise capacity compared to traditional supervised exercise [58]. The non-inferiority margin (V̇O_2_ 1.25 ml⋅kg^-1^⋅min^-1^) is clinically significant and is associated with lower cardiovascular mortality [59].

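### The primary ANCOVA admits covariates beyond baseline VO2max, age and ethnicity only if they are significant at 5% in the trial data, so the confirmatory model is partly data-driven; the effect on the one-sided 2.5% error rate is modest

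*Protocol article*

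**What the plan says.** The Statistical analysis section of the protocol article states that an "Analysis of covariance (ANCOVA) regression model will be used to evaluate the main treatment effect on the primary outcome". The model adjusts for the baseline value of the outcome, age and ethnicity, and then for "other potential confounding factors (if they are statistically significant at 5% level"). The section adds that other continuous outcomes will be handled in a similar way.

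Three other statements bear on this:

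- Randomisation and blinding: allocation is "at a 1:1 ratio, stratified by study site and sex". Neither site nor sex is named as a covariate in the Statistical analysis section.
- Sample size calculation: the trial is planned for "80% power at 2.5% level of significance (one-sided").
- Discussion: the non-inferiority margin is "1.25 ml⋅kg^-1^⋅min^-1".

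**The concern.** Baseline differences between randomised arms arise by chance, so they are not confounding in the usual sense. A p-value from the trial's own data is a poor reason to adjust. Covariates are better chosen beforehand, because they are expected to predict the outcome or because they were used in the randomisation. Here the two factors used in the randomisation have no guaranteed place in the model. Site is not a formality: exercise tests are run at two clinics, and lipids and glucose are measured on different analysers at each.

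The rule also affects inference. The limit compared with the margin comes from a model settled after the data are seen, and the usual standard error takes no account of that step. If covariates are kept because they explain the outcome in this sample, the residual variance is somewhat understated. A result close to the margin could then depend on which covariates passed the screen. The same rule applied to each continuous secondary outcome could give each of them a different covariate set.

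**Working it through.** **1. Inputs from the protocol.** One-sided alpha 0.025, power 80%, SD of change 2.7 and 162 participants (81 per group), a figure that "has been inflated to allow for 10% loss to follow up" (Sample size calculation); margin 1.25 (Discussion).

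**2. The plan's own sample size.** With a true difference of zero, n per arm = 2 × (1.960 + 0.842)² × 2.7² / 1.25² = 2 × 7.851 × 7.29 / 1.5625 = 73.3, rounded up to 74. Dividing by 0.9 gives 83 per arm, 166 in total. The stated 162 is within 3% of this. Without the intermediate rounding, 73.3 / 0.9 = 81.4, close to the stated 81. Expected evaluable: 0.9 × 162 = 145.8, about 73 per arm. The standard error is then 2.7 × √(2/73) = 0.447, and 1.25 / 0.447 − 1.960 = 0.84, so power is 79.9%. The planned size is reproduced, and 73 per arm is used below.

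**3. Error rate at the margin.** Data were simulated with a true difference of −1.25, SD 2.7 and 73 per arm. The ANCOVA had three covariates always included and K further candidates. Non-inferiority is declared when (estimate + 1.25) / SE exceeds the 97.5% point of the t distribution. K and the correlation r of each candidate with the outcome are assumptions, because the protocol gives neither.

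*Outcome screening: each candidate is tested for association with the outcome and added if p < 0.05.* 20,000 runs per row; Monte Carlo SE √(0.025 × 0.975 / 20,000) = 0.11 percentage points.

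| K | r | Three covariates only | All candidates forced in | Screened at 5% |
|---|---|---|---|---|
| 5 | 0 | 2.41% | 2.32% | 2.51% |
| 5 | 0.15 | 2.42% | 2.37% | 2.68% |
| 5 | 0.30 | 2.56% | 2.55% | 2.61% |
| 10 | 0 | 2.48% | 2.53% | 2.61% |
| 10 | 0.15 | 2.44% | 2.34% | 2.84% |
| 10 | 0.25 | 2.54% | 2.46% | 2.81% |

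Both fixed models stay within simulation error of 2.5%; the largest departure is (2.50 − 2.32) / 0.11 = 1.6 SE. The largest screened value is (2.84 − 2.50) / 0.11 = 3.1 SE above nominal, so the excess is real but small.

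*Other readings of the rule.* 10,000 runs per row; Monte Carlo SE about 0.16 points. Because the error rate at the margin depends only on the shifted difference, these runs test against zero.

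| K | r | Backward elimination at 5% | Entry if baseline imbalance p < 0.05 |
|---|---|---|---|
| 5 | 0 | 2.44% | 2.42% |
| 5 | 0.30 | 2.50% | 1.82% |
| 10 | 0 | 2.92% | 2.71% |
| 10 | 0.25 | 2.38% | 1.51% |

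*A separate simulation* with the same arm size, total SD 2.7 and 5 to 10 candidates gave 2.4 to 2.6% for the fixed model, 2.7 to 3.2% for outcome screening and 2.1 to 2.6% for imbalance screening.

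**4. Reading the results.** Taking both simulations of one-at-a-time outcome screening together, the error runs from about 2.5 to 3.2%. Backward elimination falls in or just below that range. Imbalance screening shows no clear inflation, and it is conservative when the covariates are prognostic.

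**The case against.** The strongest reply is that little is at stake. The core of the model is fixed, an entry rule is stated, and applying it mechanically moves the error rate by a fraction of a percentage point under inputs that the protocol does not supply. The list of candidates and the screening procedure are details that a condensed article may leave to an analysis plan. Most of this stands. The missing list is not held against the protocol. But the 5% criterion is stated, and an analysis plan that merely listed the candidates would leave it in force.

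Four stronger readings are tempting, and the protocol does not support them.

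- *All covariates are chosen by significance.* The grammar could allow the bracket to govern the whole list, but its natural reach is the unnamed other factors.
- *Selection makes the interval too narrow.* This is true on average under outcome screening but false under imbalance screening, and the wording fits either.
- *The error could reach 4 to 8%.* Simulations in which the most favourable of several models is reported gave 2.7 to 4.2% or 3.1 to 7.7%, depending on how many models were on offer. The protocol describes one model and does not allow a choice among results, so those figures are not a property of its rule.
- *Outcome screening alone goes well above 3%.* Values up to 3.9% were obtained with a coefficient of 0.4 per SD, but the upper end needs 10 to 15 independent prognostic factors beyond the three named. Adding 15 such factors to a residual SD of 2.7 gives a total SD of √(7.29 + 15 × 0.16) = 3.1, more than the 2.7 that the protocol assumes for the change itself.

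**Conclusion.** The point holds in a limited form. The protocol sets a significance rule for part of its confirmatory model. That is the wrong basis for adjustment in a randomised trial, and it leaves site and sex without a guaranteed place. The one-sided 2.5% level is therefore not guaranteed, but nothing here shows gross inflation. With 5 to 10 assumed candidates, the excess under one-at-a-time outcome screening is between nothing and about 0.7 points (3.2 − 2.5). Under imbalance screening the test is nominal to conservative. These sizes rest on 73 evaluable per arm, SD 2.7, independent candidates and correlations with outcome of 0 to 0.3. It does not invalidate the trial. It is worth correcting because planned power is only about 80%, so a limit close to the margin is plausible, and a reader should then be able to see that the conclusion did not depend on which covariates were kept.

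**What to change.** In the Statistical analysis section, delete the clause that admits further covariates when they are significant. State the primary model in advance as treatment, baseline VO2max, age, ethnicity, site and sex. For each continuous secondary outcome use the same set, with that outcome's own baseline value in place of baseline VO2max. Report any model with further covariates only as a labelled sensitivity analysis.

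The change is a sentence or two of wording. Site (two levels) and sex take two degrees of freedom from about 146 evaluable participants. The sample size does not change, and the simulated error rate with a fixed covariate set was 2.3 to 2.6%.

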## Discussion

This novel study evaluates a supervised exercise program delivered via a mobile phone and sensor system compared to a traditional model of supervised exCR. Remote monitoring may offer the same benefits as supervised gym-based programs, but is potentially more accessible to a broader range of patients and is cost-effective.

The protocol, in accordance with the SPIRIT statement, incorporates findings from recent mobile and telehealth systematic reviews, with the aim of building on this empirical evidence. The REMOTE-CR trial includes an objective assessment of maximal cardiorespiratory fitness, which is the gold standard measurement following exCR. It also includes objective assessment of physical activity, which was lacking in previous research [34].

The non-inferiority trial design is most suitable because it is unlikely the REMOTE intervention will result in substantially greater improvement in exercise capacity compared to traditional supervised exercise [58]. The non-inferiority margin (V̇O_2_ 1.25 ml⋅kg^-1^⋅min^-1^) is clinically significant and is associated with lower cardiovascular mortality [59].
